**Study visits**	
Day 0	• Informed consent obtained • Mother-infant identification number assigned • Infant and maternal contact information, sociodemographic characteristics, current clinical status, and medical history obtained • Infant weight, length, mid-upper arm circumference (MUAC), head circumference measured • Infant physical examination performed • Infant stool sample collected • Maternal weight, height, and MUAC measured • Randomization completed if eligible for randomization
Day 4	• Infant weight, length, MUAC, head circumference measured • Infant hemoglobin measured • Infant and household dietary survey administered • Infant adverse events recorded • Maternal hemoglobin measured • Randomization completed if not already randomized and eligible for randomization
Day 14	• Infant weight, length, MUAC, head circumference measured • Infant dietary survey administered • Infant adverse events recorded
Day 30	• Infant weight, length, MUAC, head circumference measured • Infant stool sample collected • Infant and household dietary survey administered • Infant adverse events recorded • Maternal breast milk sample collected
Day 60	• Infant weight, length, MUAC, head circumference measured • Infant and household dietary survey administered • Infant adverse events recorded • Milk transfer assessed
Day 180 (study exit)	• Infant weight, length, MUAC, head circumference, skin folds measured • Infant stool sample collected • Infant and household dietary survey administered • Infant adverse events recorded • Maternal weight, height, and MUAC measured

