### Randomization and study procedures

Following enrollment, trained study staff will perform day 0 study procedures (Table 1) according to the most recently approved version of the protocol (current V.2.1, January 2021). Randomization to intervention group will be stratified by country and by weight at time of randomization (day 0 weight 2000–2249g; day 0 weight 2250–2499g; day 4 weight 2250–2424g; day 4 weight 2425–2599g), with 1:1 randomization within each stratum. If the enrolled infant weighs 2000–2499g on day 0, the dyad will be randomized on day 0. If the enrolled infant weighs 2500-2885g on day 0, the dyad will not be randomized on day 0; no intervention will be given on day 0 and the study team will follow the infant and weigh the infant again on day 4. If the enrolled but not yet randomized infant weighs <2600g on day 4, the dyad will be randomized on day 4; however, if the enrolled but not yet randomized infant weighs ≥2600g or has a weight loss ≥10% of birth weight on day 4, the dyad will exit the study. Random allocation will be accessed through a password-protected secure program (randomize.net) on a study device. While study staff and mothers will not be blinded to intervention assignment, the study staff will have no foreknowledge of intervention assignment. Participants will be enrolled with complete concealment of intervention so that both study staff and participants will learn of intervention allocation upon randomization.

Various mitigation measures will be put in place to reduce the possibility that the study’s conduct will impact the acceptability or distribution of formula within the postpartum ward or healthcare provider counselling and support for breastfeeding. First, all formula will be kept out of sight of patients and healthcare providers in a locked cabinet or locked room unless in active use by study staff or participants. Second, study activities will occur in a private room within in the hospital or in the participant’s home rather than on the postpartum ward. Third, prior to randomization, formula will be stored in an opaque container, so that only mothers who are randomly assigned to the study intervention will see it. Fourth, the study will not advertise for participants and will not distribute any materials to participants other than those required by the respective ethics committees.

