### Sample size

In each country, trained study staff will weigh up to 1,064 infants to identify and randomize 72 with birth weight ≤2500g and 90 who weigh <2600g on day 4. With respect to the primary aim, determining the impact of formula on WAZ at 30 days of infant age, the anticipated sample size of 324 dyads (144 LBW infants and 180 infants with low weight on day 4 under equal randomization) will provide 80% or greater power per weight stratum for intervention group comparison to detect a difference of 0.20 with respect to the outcome of WAZ at day 30 for the entire study cohort after accounting for up to 20% loss to follow-up. This sample size will also allow the estimation of the mean difference between WAZ at day 30 and WAZ at birth with 0.17 and 0.15 standard errors by intervention group, respectively, for the entire study cohort. Including both mothers and infants, the total sample size for the randomized trial is anticipated to be 324 mothers and 324 infants, or 648 individual participants in total.

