### Statistical analyses

Our primary analysis will be intention-to-treat which will inform the primary global health policy question of whether recommending formula improves infant growth. In order to account for our planned stratified randomization, we will use a permutation test, permuting the infant feeding intervention assignment within the infant weight stratum, to determine the effect of formula on the primary outcome of WAZ at 30 days of infant age as well as on the secondary and exploratory outcomes of WLZ at 30 days, WAZ, WLZ and LAZ through 6 months, intestinal microbiota at 30 days of age, breastfeeding duration, and receipt of non-breast milk dietary intake between birth and 6 months of age.

To determine *B*. *infantis* abundance, stool samples will be shipped to University of California, Davis for analysis and assessed by 16S rRNA gene sequencing. Samples found to have sequences from the *Bifidobacteriaceae* family will be further subjected to analysis of bifidobacterial species-specific terminal restriction fragment length polymorphisms (Bif-TRFLP) to identify specific species of *Bifidobacterium*. Statistical differences in *B*. *infantis* abundance between supplemented and unsupplemented infants, while accounting for strata, will be assessed by mixed linear modeling. In additional exploratory analyses, we will use cluster and eigenstructure analyses (e.g., principal component analysis) for descriptive analysis of 16S rRNA gene abundance data, followed by adonis permutation tests for significance of associations with continuous or factor variables or Mantel tests for associations between distance matrices. For example, feeding intervention group is an important factor variable; a significant association of the 16S rRNA gene profile with group membership would suggest an effect of formula on microbiota. Additional exploratory analyses will be undertaken with supervised machine-learning approaches, in order to identify new and unexpected features unique to the intestinal environment of formula recipients. For example, random forests will be used to identify important features separating the microbiotas of formula from EBF recipients.

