### Safety

There will be close safety monitoring of all enrolled and randomized dyads. Each participating infant will be evaluated by a study clinician at each study visit and if necessary, referred to local healthcare providers for management. Stringent COVID-19 precautions to mitigate all potential exposures will be taken throughout the study. Visits will be conducted either at the participant’s home or at the study site to ensure timely assessment. Every effort will be made to trace all dyads in the study for the final outcome assessment. An emergency number will be provided to all study participants so that an on-call clinician can be reached at any time during study participation. As needed, infants in the study will be seen at interim visits and referral facilitated for those with concerning signs or symptoms or measured weight loss ≥10% of birth weight or for any other necessary care. All adverse events will be assessed and managed in accordance with standard clinical practice at the study sites and documented by the study team. Infants with an adverse event will be followed and treated until the adverse event is resolved or stabilized. All serious adverse events occurring after randomization will be reported to the principal investigator and a study safety medical officer for review within 24 hours of the event. Serious adverse events occurring after randomization will be regularly reviewed by the study medical monitor and compiled into reports for the co-investigators. An independent 5-person data safety and monitoring board (DSMB) will review cumulative safety and study conduct data through two formal interim analyses. At a minimum, safety data presented to the DSMB will include summaries of data on adverse events, serious adverse events, and adherence rates among randomized infants. The DSMB will consider recommending to stop the trial prior to maximum enrollment if they determine there are safety concerns.

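### Receipt of non-breast-milk intake is counted from birth, but 56% of infants are randomised only on day 4, so feeds before allocation can dilute this secondary or exploratory comparison

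*Protocol article*

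**What the plan says.** The Statistical analyses section of the Protocol article lists the secondary and exploratory outcomes on which the effect of formula is to be determined by a permutation test within weight stratum. The last of them is "receipt of non-breast milk dietary intake between birth and 6 months of age". The window is thus stated, and it opens at birth for every infant.

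The Randomization and study procedures section sets two times of allocation. Infants weighing 2000–2499 g on day 0 are randomised that day; Table 1 requires them to be under 6 hours old. For infants weighing 2500–2885 g, "the dyad will not be randomized on day 0; no intervention will be given on day 0". They are weighed again later: "If the enrolled but not yet randomized infant weighs <2600g on day 4, the dyad will be randomized on day 4".

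The Sample size section plans an "anticipated sample size of 324 dyads", made up of "144 LBW infants and 180 infants with low weight on day 4 under equal randomization".

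In Table 1 (Study visits), the first dietary survey appears at day 4: "Infant and household dietary survey administered". Randomisation of infants not yet allocated is listed at the same visit. Nothing in the article removes feeds given before allocation from the outcome.

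**The concern.** A between-arm comparison of an outcome accumulated over time should start when the arms come into existence. Here it does so, to within hours, for the low-birth-weight infants. For the day-4 stratum, which is the larger one, the window opens about four days earlier. A feed of water or anything else on days 0–4 would make such an infant an event before it has an assignment. If the outcome is ever/never, that infant can no longer show any effect of its arm.

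Such feeds are plausible on the document's own account. The Limitations and bias section expects that some infants under a recommendation of exclusive breastfeeding will be supplemented, and the control regimen counts water as a departure. Nothing in the day-4 eligibility criteria in Table 1 excludes an infant who has already been given other feeds.

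At stake is the size and precision of one secondary or exploratory comparison. The issue concerns feeds before allocation in both arms, not the assigned study formula.

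**Working it through.** **Share of infants affected.** The Sample size section states, per country, "randomize 72 with birth weight ≤2500g and 90 who weigh <2600g on day 4". With two countries:

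- day-0 stratum: 2 × 72 = 144
- day-4 stratum: 2 × 90 = 180
- total: 144 + 180 = 324, which reproduces the stated figure
- w = 180/324 = 0.556, the planned share randomised on day 4

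**Dilution for an ever/never outcome.** Notation:

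- p₁, p₂ = probability of receipt after randomisation in the two arms, taken as equal across strata
- q = proportion of day-4-stratum infants with a non-breast-milk feed before randomisation. It is the same in both arms in expectation, because no assignment exists yet. It is not given in the document; 10%, 20% and 30% are assumed.

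If early and later feeding are independent, the risk counted from birth in the day-4 stratum is q + (1 − q)p. Over the whole trial it is

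(1 − w)p + w[q + (1 − q)p].

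Taking the difference between arms, the term wq cancels and

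RD from birth = (1 − wq)(p₁ − p₂) = (1 − 0.556q) × RD from randomisation.

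| q (assumed) | Factor, day-4 stratum (1 − q) | Factor, whole trial (1 − 0.556q) | Trial-wide loss | A 15-point difference becomes |
|---|---|---|---|---|
| 10% | 0.90 | 0.944 | 6% | 14.2 points |
| 20% | 0.80 | 0.889 | 11% | 13.3 points |
| 30% | 0.70 | 0.833 | 17% | 12.5 points |

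The 15 points are illustrative (40% vs 25%).

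**What this can cost in power.** Take illustrative post-randomisation risks of 50% vs 33%, the planned 20% loss to follow-up (324 × 0.8 / 2 = 129.6 per arm), two-sided 0.05 (assumed) and a simple comparison of two proportions. Power is 79.7% counted from randomisation. Counted from birth it is 74.1%, 68.5% and 62.7% at q = 10%, 20% and 30%.

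**When the loss disappears.** If every early-fed infant would also be fed after randomisation whatever its arm, it is an event under either start point. The two differences then coincide and the loss is zero. The table is therefore the independence case; positive dependence between early and later feeding moves the factor towards 1.

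**The case against.** **The form of the outcome is not stated.** The article does not say whether receipt is ever/never, per visit or an amount. The outcome is named only at the end of a list and appears neither among the Table 1 endpoints nor in the Outcomes section. The survey form is not shown. Analysed per visit, the day-4 survey would not contaminate later ones. This stands as a condition on the size of the problem. It does not remove the start point, which the article does state.

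**The test is not damaged.** A reader might infer that a chance imbalance in early feeds would be mistaken for an effect of the recommendation. The document does not support that. Assignment is permuted within weight strata, and those strata separate day-0 from day-4 infants. Feeds before allocation cannot depend on assignment, and their chance imbalance is part of the permutation distribution. Type I error is unaffected; what remains is dilution and noise.

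**There is no contradiction with the safety rule.** The Safety section says "All serious adverse events occurring after randomization will be reported", and a reader might take this as a conflicting start point. It is a reporting duty, not an outcome window, and the two need not agree.

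**Study formula may count as an event.** The article does not say. If it does, the formula arm is near 100% by design. The same factor applies, but the contrast is then so large that a modest dilution hardly matters.

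**Age-based windows are the document's habit.** WAZ at 30 days is indexed by age, and feeding since birth is a fair description of infants. But WAZ at 30 days is a status at one age, whereas receipt over an interval accumulates and carries the time before allocation with it.

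**Conclusion.** The point holds as a minor one. The stated window starts before randomisation for a planned 56% of infants, in an outcome meant to show the effect of formula. If the outcome is analysed as ever/never or cumulative receipt, and early and later feeding are independent, the trial-wide difference shrinks by about 6%, 11% or 17% at q = 10%, 20% or 30%.

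A reader might quote the loss as 10–30%. That applies only within the day-4 stratum; the infants randomised on day 0 have almost no time before allocation. All these figures rest on an assumed q, and the loss approaches zero if early feeds are rare, if early-fed infants would be fed later anyway, or if the analysis is per visit.

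The permutation test remains valid, there is no systematic bias between arms beyond the dilution, and the primary WAZ analysis is untouched.

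**What to change.** Define the outcome as receipt of non-breast-milk intake between randomisation and 6 months of age. For infants randomised on day 4, treat that day's dietary survey as baseline: tabulate it by arm or adjust for it, and do not count it towards the outcome. For infants randomised on day 0, the day-4 survey remains outcome data.

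The cost is one phrase in the Statistical analyses section, with no new visit or data item, since the day-4 survey is already collected separately. The downside is that the tested outcome no longer describes feeding since birth in the day-4 stratum; the baseline table can still report it.

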## Ethics and dissemination

### Ethical approvals and consent

The study will be conducted in accordance with the ICH GCP and the Declaration of Helsinki 2008. The protocol and other relevant study documents were approved by the UCSF Institutional Review Board (19–29405); the Guinea-Bissau National Committee on Ethics in Health (Comite Nacional de Etica na Saude, 075/CNES/INASA/2020); the Higher Degrees, Research and Ethics Committee of Makerere University (871); and the Uganda National Council of Science and Technology (HS1226ES). Local clinicians will inform mothers about the study and refer those who are interested to study staff. Trained study staff will review the birth record to confirm eligibility for screening and then initiate contact with the mothers. Written informed consent will be obtained in the local language by trained study staff from eligible study participants prior to enrollment. Potential participants will have adequate time to ask questions and a comprehension checklist will be administered to ensure participant understanding.

To address the risk that the conduct of this study could result in changes to current infant feeding recommendations or practices at the local hospitals or any violation to the International Code of Marketing of Breast-milk Substitutes, targeted mitigation measures will be undertaken. First, the importance of frequent, on-demand breastfeeding will be emphasized to all study participants. Second, the study will not advertise for recruitment, but instead will rely on referrals from hospital staff who are educated about the benefits of breastfeeding. Third, informed consent will provide all potential participants with information about the risks of formula supplementation. Fourth, all formula will remain securely stored in a locked storage unit unless in active use. Fifth, formula use will be demonstrated only to mothers in the small-volume formula supplementation group, and formula bottles will remain concealed in an opaque container until randomization occurs. Any protocol violations will be reported to the appropriate ethics committees.

### Safety

There will be close safety monitoring of all enrolled and randomized dyads. Each participating infant will be evaluated by a study clinician at each study visit and if necessary, referred to local healthcare providers for management. Stringent COVID-19 precautions to mitigate all potential exposures will be taken throughout the study. Visits will be conducted either at the participant’s home or at the study site to ensure timely assessment. Every effort will be made to trace all dyads in the study for the final outcome assessment. An emergency number will be provided to all study participants so that an on-call clinician can be reached at any time during study participation. As needed, infants in the study will be seen at interim visits and referral facilitated for those with concerning signs or symptoms or measured weight loss ≥10% of birth weight or for any other necessary care. All adverse events will be assessed and managed in accordance with standard clinical practice at the study sites and documented by the study team. Infants with an adverse event will be followed and treated until the adverse event is resolved or stabilized. All serious adverse events occurring after randomization will be reported to the principal investigator and a study safety medical officer for review within 24 hours of the event. Serious adverse events occurring after randomization will be regularly reviewed by the study medical monitor and compiled into reports for the co-investigators. An independent 5-person data safety and monitoring board (DSMB) will review cumulative safety and study conduct data through two formal interim analyses. At a minimum, safety data presented to the DSMB will include summaries of data on adverse events, serious adverse events, and adherence rates among randomized infants. The DSMB will consider recommending to stop the trial prior to maximum enrollment if they determine there are safety concerns.

### Possible risks

There are potential risks to study participation. This is a randomized trial that is investigating the efficacy of formula compared to EBF, and it is possible that formula may increase the risk of diarrhea, infectious diseases, and breastfeeding cessation, exposing infants in the formula group to increased risk of adverse events, hospitalization or death compared to infants in the EBF group. It is also possible that formula avoids underweight wasting and stunting in early infancy and that infants in the EBF group could experience higher rates of growth failure, with an increased risk of adverse events, hospitalization, or death. Diarrhea, infectious diseases, breastfeeding cessation, and growth failure are common risks in infancy in LMIC, and both breastfeeding with supplementation and EBF are common. For this reason, the risks to infant study participants are not anticipated to differ from the ordinary risks of infancy. The purpose of this study is to determine if the incidence of any of these risks differs between the feeding groups, with the hypothesis being that these metrics are improved in the formula group compared to the EBF group. Furthermore, the study was carefully developed and pragmatically designed with inclusion and exclusion criteria to allow results as generalizable as possible without putting infants with severe illness at risk and a robust safety monitoring scheme will be in place. Infants most at risk of adverse consequences from formula will be excluded from this study, including those with birth weight <2000g, those with weight loss ≥10% on day 4, those with congenital abnormalities, and those with WHO danger signs. To further ensure safety, if any medical or safety issues are identified, study staff will confirm that study participants have been appropriately and expeditiously referred to local healthcare providers for management.

Recognizing that some study participants may not come back for the follow-up visits, trained study staff will attempt to locate infants who miss their follow-up appointments and conduct these visits in the home. We will also ensure that study staff take the time to educate mothers on the importance of breastfeeding, adhering to the assigned intervention, and follow-up.

### Dissemination

We plan to disseminate study results in peer-reviewed journals and international conferences, targeting those involved in the clinical care of infants in low-resource settings as well as those who develop and advise on policies and guidelines in those settings. The trial is registered with ClinicalTrials.gov (registration number NCT04704076).

### Efforts towards a rigorous protocol

Dedicated study staff trained in GCP and study-specific procedures will follow enrolled dyads to assure the protocol and standard operating procedures are followed and data are accurately collected. Standardized study-specific training, supervision, and oversight will be undertaken to ensure quality, consistency, and harmonized trial procedures and implementation. Regular monitoring will be provided by the co-investigators to assess compliance with human subjects and other research regulations and guidelines, adherence to the study protocol and procedures, and quality and accuracy of data collected.

